**Duration of follow-up**

Each patient will be followed-up until hospital discharge. Information about the status (dead/alive) of patients who are discharged from hospital before 30 days will be sought on Day 30 from randomisation.

**Concomitant medications**

Concomitant diseases or conditions will be treated according to the principles of Good Clinical Practice and according to clinical judgement of the attending physician. There will be no restrictions on concomitant treatments for the underlying disease to be given to patients enrolled in this study.

Any relevant health intervention received by participants 24 hours before the randomisation and during the study period will be recorded.

**Criteria for discontinuing or modifying allocated interventions**

LMWH administration will start at the moment of randomization and will last until the hospital discharge, or up to the occurrence of any event included in the primary outcome.

Participants who during their hospital stay develop any new clinical condition, which require anticoagulant or antiplatelet treatment, such as atrial fibrillation and/or substitution of heart valves, will discontinue the allocated intervention and will be excluded from the study.

Discontinuation or modification of allocated interventions can also be warranted by the occurrence of one of the following events: any AE, including clinically relevant, non-major bleeding or clinically significant laboratory abnormality that, in the opinion of the Investigator, warrants the subject’s discontinuation, temporary or permanent, of study protocol-directed care.

Reasons for discontinuation or modification of allocated interventions and their dates will be collected and reported in the eCRF.

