**2.4 OUTCOMES**

**2.4.1 Primary Efficacy Endpoint:**

Clinical worsening, defined as the occurrence of at least one of the following events, whichever comes first:

1. Death
2. Acute Myocardial Infarction [AMI]
3. Objectively confirmed, symptomatic arterial or venous thromboembolism [TE]
4. Need for either non-invasive - Continuous Positive Airway Pressure (Cpap) or Non-Invasive Ventilation (NIV) - or invasive mechanical ventilation for patients, who are in standard oxygen therapy by delivery interfaces at randomisation
5. Need for invasive mechanical ventilation for patients, who are in non-invasive mechanical ventilation at randomisation

Time to the occurrence of each of these events will be recorded.

Clinical worsening will be analysed as a binary outcome as well as a time-to-event one.

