**4.2 Statistical Methods**

All patients enrolled in the study will be entered in the full analysis set independently of his/her treatment time. The intention to treat population will be considered for primary analysis. A descriptive statistical analysis will be carried out to summarise every relevant variable. At baseline, categorical data will be summarised by using counts and percentages, whilst continuous variables will be presented using the number of patients, mean, standard deviation, median, minimum, and maximum. Comparison between binary outcomes will be performed by using Relative Risks (RRs), whereas for continuous data, the difference of means (DMs) will be used. Comparisons involving time to event data will be displayed by using Kaplan-Maier survival curves and summarised by Hazard Ratios (HRs).

All measures of association will be presented with their 95% confidence interval. A result will be considered as statistically significant if its p-values will be less than 0.05 (5%).

The analyses will be performed by using STATA software.

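### Excluding randomised patients who develop a new need for anticoagulant or antiplatelet treatment contradicts the protocol's intention-to-treat and follow-up rules

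*Protocol*

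**What the plan says.** The section on criteria for discontinuing or modifying allocated interventions covers participants who, during their stay, "develop any new clinical condition, which require anticoagulant or antiplatelet treatment, such as atrial fibrillation and/or substitution of heart valves". It gives two instructions for them: they "will discontinue the allocated intervention and will be excluded from the study".

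Three other parts of the protocol bear on this:

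- **Section 4.2, Statistical Methods:** "All patients enrolled in the study will be entered in the full analysis set independently of his/her treatment time", and then "The intention to treat population will be considered for primary analysis".
- **Duration of follow-up:** "Each patient will be followed-up until hospital discharge". For patients who leave hospital before day 30, vital status is sought at day 30.
- **Section 2.4.1:** "Acute Myocardial Infarction [AMI"] and "Objectively confirmed, symptomatic arterial or venous thromboembolism [TE"] are components of the primary endpoint.

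The sentence just before the exclusion clause deals with primary-outcome events separately. Enoxaparin runs to discharge "or up to the occurrence of any event included in the primary outcome", and nothing is said there about leaving the study. The section on duration of treatments also lists infarction and thromboembolism as events that end assigned enoxaparin. It then keeps collecting antithrombotic treatment data until discharge or death.

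**The concern.** Stopping the drug and leaving the study are written as two separate instructions, so the second cannot be read as a restatement of the first. A site that obeys it stops collecting outcomes on a randomised patient. The trigger arises after randomisation, is judged by staff who know the arm, and may itself depend on heparin dose. The patients removed are therefore not a random subset, and the two arms may lose different kinds of patient.

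The protocol's own examples, new atrial fibrillation and valve replacement, are not endpoint events. Such a patient may still be free of any primary event when excluded. A later death or start of ventilation would then be missing from the primary endpoint as well as from the secondary and bleeding endpoints and day-30 mortality. A statistical analysis plan cannot recover data that sites were told not to collect.

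There is also a drafting risk. The trigger is any new condition, its examples are illustrative, and no exception is made for endpoint events. Exclusion criterion 9 lists venous thromboembolism beside atrial fibrillation as an indication for anticoagulation, so the words can be read to cover it. That infarction calls for antiplatelet treatment is general knowledge, not stated in the protocol.

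**Working it through.** **1. The rules side by side.** Take a randomised patient who develops atrial fibrillation on day 4 and dies in hospital on day 12, with no earlier primary event.

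- Under the discontinuation section, the patient leaves the study on day 4 and the death is not a study outcome.
- Under the follow-up section, the patient is followed to the end of the hospital stay, so the death is recorded.
- Under section 4.2, the patient is analysed in the allocated arm and the death is a primary event.

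The first rule excludes the other two. No other section reconciles them. This contradiction needs no arithmetic.

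**2. The protocol's sample size.** Inputs from section 2.6: 300 patients 1:1, two-sided alpha 0.05, control rate 25% to 30%, 50% relative reduction, 80% power. With pooled variance and no continuity correction,

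n per arm = [1.96·√(2p̄(1−p̄)) + 0.842·√(p₁(1−p₁)+p₂(1−p₂))]² / (p₁−p₂)²

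- 25% vs 12.5%: n = 152 per arm, total 304. Power at 150 per arm is 79.5%.
- 30% vs 15%: n = 121 per arm, total 242. Power at 150 per arm is 87.9%.

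The stated 300 reproduces at the lower end of the control-rate range, where there is no slack for lost patients. If 5% or 10% of patients dropped out at random (assumed), leaving about 143 or 135 per arm, power at the 25% control rate would be 77.6% or 75.2%.

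**3. What non-random removal could do.** This step illustrates the broadest reading, in which patients whose first event is thromboembolism (TE) leave both numerator and denominator. The background section gives venous thromboembolism on general wards as 0% to about 8%. The 8% control rate below is the top of that range, and treating all of it as first events is an assumption. So are the high-dose rates.

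With 150 per arm, primary rate p and TE-first rate t in an arm, the rate among those left is (p − t)/(1 − t) on 150(1 − t) patients. Power = Φ[(d − 1.96·SE₀)/SE₁], where d is the difference in rates, SE₀ is pooled and SE₁ is unpooled.

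Control rate 25%, true relative risk (RR) 0.50, so 37.5 and 18.75 expected events:

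| TE-first, control / high dose | Control left | High dose left | RR | Power |
|---|---|---|---|---|
| none removed | 37.5/150 = 25.0% | 18.75/150 = 12.5% | 0.50 | 79.5% |
| 2% / 1% | 34.5/147 = 23.5% | 17.25/148.5 = 11.6% | 0.49 | 76.7% |
| 8% / 2% | 25.5/138 = 18.5% | 15.75/147 = 10.7% | 0.58 | 46% |
| 8% / 4% | 25.5/138 = 18.5% | 12.75/144 = 8.9% | 0.48 | 66% |
| 8% / 6% | 25.5/138 = 18.5% | 9.75/141 = 6.9% | 0.37 | 83% |
| 8% / 8% | 25.5/138 = 18.5% | 6.75/138 = 4.9% | 0.26 | 94% |

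With a 30% control rate and 8% TE-first in controls, the RR runs from 0.55 (power 64%, high dose 2%) to 0.32 (power 96%, high dose 8%). Removal can understate or exaggerate the benefit. The direction depends on how dose affects the removed events, which the trial cannot know beforehand.

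**The case against.** A reader might infer that the protocol plans to drop patients with infarction or thromboembolism from the primary analysis. Read as a whole, it does not support that. The preceding sentence gives primary-outcome events their own rule. The section on treatment duration treats both events as ending treatment and then keeps collecting data, which would make little sense for patients who had left. Section 2.4.1 counts both, and the examples in the clause are not endpoint events. The endpoint is also met by whichever event comes first, so a patient whose first event is thromboembolism has already reached it when the clause applies. Losing that event would mean deleting it from the analysis set, which section 4.2 rules out. All of this stands: for these events the fault is loose wording, not an evident rule.

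A reader might also infer that power would fall to about 46%. That figure takes the top of a 0% to 8% range, treats every thromboembolism as a first event, and pairs it with the most favourable of the assumed high-dose rates. Patients ventilated before their thromboembolism have already had a primary event, so the true first-event share may be smaller. Other rows of the same table show power rising.

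None of this rescues the clause for new indications that are not endpoint events. Section 4.2 states the right analysis rule, but it cannot supply outcomes that were never collected.

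**Conclusion.** The contradiction is certain and rests on the text alone: one clause removes randomised patients whom section 4.2 analyses and the follow-up section follows. It should be corrected, because it decides whose outcomes enter the primary comparison and selects them on a post-randomisation event in an open-label trial. The number affected cannot be derived from the protocol, which gives no rate for new anticoagulant or antiplatelet indications.

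The reach to infarction and thromboembolism is a secondary point about wording. Its numerical range holds only if such patients were actually removed and only under the assumed rates: RR about 0.26 to 0.58 and power about 94% to 46% with 8% TE-first in controls and a 25% control rate, shrinking to nothing as the rate approaches 0%. It is an illustration of uncontrolled bias and not a forecast.

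**What to change.** In the section on discontinuing or modifying allocated interventions, delete the words that exclude the patient from the study. Say instead that the patient remains in the study, is followed to hospital discharge and day 30, and is analysed in the allocated arm under intention to treat, with the discontinuation and the new treatment recorded in the eCRF. Add one sentence stating that myocardial infarction and thromboembolism always count as primary-endpoint events. The rule on stopping study treatment is not touched by this change.

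The cost is about two sentences. The protocol already requires reasons and dates of discontinuation in the eCRF, antithrombotic treatment after interruption, follow-up to discharge and day-30 vital status. The downside is some dilution of the contrast from off-protocol anticoagulation, which an intention-to-treat analysis already accepts.

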**Strategies to improve adherence to protocols**

The site PIs will take primary responsibility for training local staff and for ensuring that protocol compliance is achieved.

**2.4 OUTCOMES**

**2.4.1 Primary Efficacy Endpoint:**

Clinical worsening, defined as the occurrence of at least one of the following events, whichever comes first:

1. Death
2. Acute Myocardial Infarction [AMI]
3. Objectively confirmed, symptomatic arterial or venous thromboembolism [TE]
4. Need for either non-invasive - Continuous Positive Airway Pressure (Cpap) or Non-Invasive Ventilation (NIV) - or invasive mechanical ventilation for patients, who are in standard oxygen therapy by delivery interfaces at randomisation
5. Need for invasive mechanical ventilation for patients, who are in non-invasive mechanical ventilation at randomisation

Time to the occurrence of each of these events will be recorded.

Clinical worsening will be analysed as a binary outcome as well as a time-to-event one.

**2.4.2 Secondary Efficacy Endpoints:**

**Any of the following events occurring within the hospital stay**

1. Death
2. Acute Myocardial Infarction [AMI]
3. Objectively confirmed, symptomatic arterial or venous thromboembolism [TE]
4. Need for either non-invasive - Continuous Positive Airway Pressure (Cpap) or Non-Invasive Ventilation (NIV) - or invasive mechanical ventilation for patients, who are in standard oxygen therapy by delivery interfaces at randomisation
5. Need for invasive mechanical ventilation for patients, who are in non-invasive mechanical ventilation at randomisation
6. Improvement of laboratory parameters of disease severity, including:
   - D-dimer level
   - Plasma fibrinogen levels
   - Mean Platelet Volume
   - Lymphocyte/Neutrophil ratio
   - IL-6 plasma levels

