| **Statistical Considerations**  **& Sample Size** | **Statistical Considerations**  The efficacy will be assessed by estimating the difference between the two treatment arms in the proportion of participants experiencing clinical worsening during their hospital stay.  Safety will be assessed by estimating the difference between the two treatment arms in the proportion of participants who experience at least one bleeding event (major or non-major) during their hospital stay.  Relative risk (RR) will be used as measure of association, which will be reported with its 95% confidence interval.  The differences between the two arms in the variation of:   1. D-dimer level 2. Plasma fibrinogen levels   3) Mean platelet Volume  4) Lymphocyte/Neutrophil ratio  5) IL-6 plasma levels  at 3 time points (at randomization, at 48 hours and 96 hours) will be assessed.  These outcomes will be compared by using their mean values and summary indicators.  Overall survival, survival free from any cardiovascular event, such as Acute Myocardial Infarction [AMI], Objectively confirmed, symptomatic arterial or venous thromboembolism [TE] and survival free from need for either non-invasive or invasive mechanical ventilation will be also estimated. They will be reported by using Kaplan-Maier curves and compared by using hazard ratio (HR).  **Sample size**  300 participants will be needed to detect a relative reduction of 50% of clinical worsening. We hypothesized that the percentage of participants who experience clinical worsening in the LMWH low dose group would be around 25-30% and set an alpha error of 0.05 and beta-error of 0.20. | |
| **Treatment Schedule** | **Control group (Low Dose):** Enoxaparin (Inhixa®) 4000 IU subcutaneously once daily.  **Intervention group (High dose**): Enoxaparin (Inhixa®) 70 IU/kg subcutaneously twice daily.  Participants will receive the dose of Enoxaparin according to the protocol until the occurrence of at least one of the following events:   1. One of the events included in the primary outcome 2. Hospital discharge 3. Any adverse events and clinical condition requiring interruption of the scheduled intervention according to the judgement of the physician in charge | |

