**Mortality at 30 days**

Information about patients’ status will be sought in those who are discharged before 30 days on Day 30 from randomisation.

Time to the occurrence of each of these events will be recorded.

Each of these events will be analysed as a binary outcome and as a time-to-event one.

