**2.4.3 Physiological and Processes of care outcomes**

- Vital signs such as systolic and diastolic arterial pressure, heart rate (HR), respiratory rate (RR) and systemic body temperature will be recorded daily from inclusion until hospital discharge (censored day 28);
- Routine laboratory test parameters for organ function assessment: blood cells count, coagulative parameters (INR, PT, aPTT, fibrinogen, D-dimer), parameters for liver (AST, ALT, bilirubin) and renal function (creatinine) and interleukin 6 (IL-6) will be recorded at least at the moment of randomization, after 48 and 96 hours, then according to clinical judgement of the attending physician until hospital discharge.

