**3.0 METHODS: ASSIGNEMENT OF INTERVENTIONS**

**3.1 Allocation and blinding**

Randomisation will be centrally performed by using a secure, web-based system, which will be developed by the Methodological and Statistical Unit at the Azienda Ospedaliero-Universitaria of Modena. Randomisation stratified by 4 factors: 1) Gender (M/F); 2) Age (<75/≥75 years); 3) BMI (<30/≥30); 4) Co-morbidities (0-1/>2) with random variable block sizes will be generated by STATA software. The web-based system will guarantee the allocation concealment. The physicians involved in the study, once they have obtained the patient’s consent, will connect to the website and will register the patient that meets inclusion criteria. The system will also allow the randomisation of the patient and the arm to which he/she is allocated will appear on the monitor. The physician who performed the randomisation will communicate which dose the patient will receive to the colleagues who are in charge of administering LMWH. The information collected during the patient follow-up will be entered on the website and stored on the Hospital’s server. The local coordinator will be in charge of training the personnel involved in the study according to what is stated in the protocol. The study is conceived as open label, i.e. the patients and all healthcare personnel will be aware of the group allocation.

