**APPENDIX 2: Timeline-scheme**

| Required investigations or activities | Screening | For any treatment | | | | | | | |  |
| --- | --- | --- | --- | --- | --- | --- | --- | --- | --- | --- |
|  | Within 5 days | Day 1 | Day 2 | Day 3 | Day 4 | Day 5 | Day 7 | Day 8 | Day 9 up to hospital discharge,  or up to occurrence of death | Day 30  Only for patients discharged from hospital before 30 days |
| Clinical history | x | x |  |  |  |  |  |  |  |  |
| Informed consent Form | x |  |  |  |  |  |  |  |  |  |
| **Physical exam** | x | x | x | x | x | x | x | x | x |  |
| **Vital signs*** | x | x | x | x | x | x | x | x | x |  |
| Body weight | x |  |  |  |  |  |  |  |  |  |
| Height | x |  |  |  |  |  |  |  |  |  |
| **Performance status** | x | x |  |  |  |  |  |  | x |  |
| Eligibility criteria | x |  |  |  |  |  |  |  |  |  |
| Pregnancy Test | x |  |  |  |  |  |  |  |  |  |
| Randomization |  | x |  |  |  |  |  |  |  |  |
| **Concomitant medications** | x | x | x | x | x | x | x | x | x |  |
| **Lab Tests**** | x | x | x |  | x |  | x |  | x |  |
| **Enoxaparin (Low-Dose LMWH) every 24 hours** |  | x | x | x | x | x | x | x | x |  |
| **Enoxaparin (High-Dose LMWH) every 12 hours** |  | x | x | x | x | x | x | x | x |  |
| **Health monitoring** |  | x | x | x | x | x | x | x | x | X **^⊥^** |

* systolic and diastolic arterial pressure, heart rate (HR), respiratory rate (RR) and systemic body temperature

** blood cells count, coagulative parameters (INR, PT, aPTT, fibrinogen, D-dimer), parameters for liver (AST, ALT, bilirubin) and renal function (creatinine) and interleukin 6 (IL-6) will be recorded at least at the moment of randomization, after 48 and 96 hours, then according to clinical judgement of the attending physician until to hospital discharge

**^⊥^** Information about these patients will be sought by phone call

**APPENDIX 3: Sepsis Induced Coagulopathy (SIC) score**^1^

| Category | Parameter | 0 point | 1 point | 2 points |
| --- | --- | --- | --- | --- |
| Prothrombin time | PT-INR 4 | <1.2 | >1.2 >1.4 | >1.4 |
| Coagulation | Platelet count (x10^9^/L) | > 150 | < 150 | <100 |
| Total SOFA | SOFA 4 items (respiratory,  cardiovascular, hepatic, renal | 0 | 1 | >2 |

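### Section 2.4.2 analyses laboratory improvement as an in-hospital event, which contradicts the synopsis and rests on blood tests left to clinical judgement after 96 hours

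*Protocol*

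**What the plan says.** **Section 2.4.2, Secondary Efficacy Endpoints.** The list is introduced by "Any of the following events occurring within the hospital stay". Items 1 to 5 are clinical events. Item 6 is "Improvement of laboratory parameters of disease severity, including" five named markers. The text that closes the section, under the sub-heading on 30-day mortality, says "Time to the occurrence of each of these events will be recorded" and "Each of these events will be analysed as a binary outcome and as a time-to-event one". Nothing exempts item 6.

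**Synopsis, Statistical Considerations.** The between-arm difference in the variation of the same five markers "at 3 time points (at randomization, at 48 hours and 96 hours) will be assessed", using means and summary indicators. The survival analyses listed there contain no laboratory item. Section 4.2 assigns differences of means to continuous data.

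**Sampling.** The section on physiological and process-of-care outcomes has laboratory values recorded at least at randomisation, "after 48 and 96 hours, then according to clinical judgement of the attending physician until hospital discharge". Section 4.1 repeats this. The Appendix 2 grid also marks laboratory tests at Day 7 and from Day 9 onward, but its footnote returns to the same rule: "then according to clinical judgement of the attending physician until to hospital discharge".

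**Blinding and follow-up.** Section 3.1 states that "the patients and all healthcare personnel will be aware of the group allocation". The paragraph on duration of follow-up ends observation at discharge, so the window differs by patient.

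**The concern.** Two different endpoints carry the same name. One is a continuous change at fixed times. The other is whether, and when, an improved value is first seen at any point in the stay. The results of the two need not agree, and the protocol does not say which one counts.

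The event version has a further weakness. A laboratory improvement is seen only when blood is drawn, so the chance of ever recording one depends on how many draws a patient has. After 96 h that number depends on decisions by staff who know the allocation and on how long the patient stays, both of which arise after randomisation. If either differs by arm, the RR for ever improving can move away from 1 with no drug effect. The HR is exposed too, because the recorded event date is a test date and follow-up stops at discharge. At stake is the reading of five secondary biomarker endpoints.

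**Working it through.** **The plan's own figure.** The protocol gives no figure for the laboratory endpoints. Its only sizing figure is 300 in total for the primary endpoint (Section 2.6: two-sided 5%, 80% power, 25% to 30% in the control arm, halved by treatment). At 25% v 12.5%, without continuity correction:

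n per arm = [1.96·√(2·0.1875·0.8125) + 0.8416·√(0.25·0.75 + 0.125·0.875)]² / 0.125² = (1.082 + 0.459)² / 0.015625 ≈ 152

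That is 304 in total, so 300 reproduces closely. It is not in dispute and serves below only to set 150 per arm.

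**Step 1: one patient, no drug effect.** Suppose the baseline value and k follow-up values are exchangeable (no trend). Baseline is then the worst of the k + 1 values with probability 1/(k + 1) in the sense that matters only if all others are better; the event of interest fails only when baseline is the best of the k + 1 values, which also has probability 1/(k + 1). So

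P(at least one follow-up value better than baseline) = 1 − 1/(k + 1) = k/(k + 1)

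- k = 2 (48 h and 96 h only): 2/3 = 67%
- k = 4: 4/5 = 80%
- k = 6: 6/7 = 86%
- k = 8: 8/9 = 89%

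**Step 2: does a stricter definition remove this?** The protocol gives no threshold or variability, so these are assumptions. Simulated probability of ever reaching the required fall, with log-normal values:

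| Required fall | Within-patient log-SD | 2 tests | 4 tests | 8 tests |
|---|---|---|---|---|
| 30% | 0.3 | 31% | 45% | 58% |
| 30% | 0.5 | 45% | 60% | 73% |
| 50% | 0.3 | 9% | 15% | 22% |
| 50% | 0.5 | 26% | 38% | 51% |

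The level changes with the threshold, but the rise with the number of tests remains.

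**Step 3: two arms, no drug effect.** Assumptions: 150 per arm, two scheduled draws plus a Poisson number of extra draws, improvement defined as a 30% fall at any time, log-SD 0.4, 4,000 simulated trials per row, two-sided 5% tests.

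| Mean extra draws, arm A v arm B | Ever improved, A v B | RR | False positives, ever improved | False positives, mean change at 96 h |
|---|---|---|---|---|
| 2 v 2 | 52.7% v 52.7% | 1.00 | 5.5% | 4.3% |
| 3 v 2 | 57.1% v 52.8% | 1.08 | 12.1% | 5.2% |
| 4 v 2 | 60.7% v 52.8% | 1.15 | 29.7% | 4.4% |
| 4 v 1 | 60.8% v 47.2% | 1.29 | 68.0% | 4.7% |

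The Monte Carlo standard error near 5% is √(0.05·0.95/4000) ≈ 0.3 percentage points. With equal testing the event analysis is therefore close to nominal. The analysis at the scheduled 96 h sample stays near 5% however much later testing differs. The HR was not simulated.

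**The case against.** The strongest reply is that the workable analysis is already written. The synopsis names all five markers, fixes three time points and compares means, and Section 4.2 agrees. The binary and time-to-event sentence recurs almost unchanged after the primary and safety endpoints, so it may have been carried over without item 6 in mind. That is plausible, but it does not remove the contradiction: as written, the sentence covers every event in the list.

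A second reply is that a threshold, an assessment window and the handling of death are commonly left to a statistical analysis plan, which is not shown. Their absence is not counted here. The point rests on what the protocol does state, namely an in-hospital event with a binary and a time-to-event analysis.

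Several stronger readings are tempting and are not supported:

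- **That the endpoint will be biased.** Bias between arms needs testing or stay to differ by arm. Open-label care makes that possible, but nothing in the documents shows it.
- **That the spurious RR would be 1.25 or more.** Five tests against two would give (5/6)/(2/3) = 1.25 for any fall, but no such gap between arms is indicated.
- **That the arm doing worse is favoured.** A longer stay allows more tests, but early death shortens stay, so the direction is open.
- **That regression to the mean creates a false difference.** Under randomisation it acts on both arms alike.
- **That deaths are censored in the analysis of improvement.** The protocol does not say so.

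It is also fair to note that the Appendix 2 grid marks tests after 96 h. However, its footnote leaves them to judgement, and the column from Day 9 gives no frequency.

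**Conclusion.** The point holds for the secondary laboratory endpoints only. Section 2.4.2 and the synopsis set out incompatible analyses of the same five markers, and the event version is the one that the sampling schedule supports poorly. That the chance of ever improving rises with the number of tests follows from the definition and held for every threshold tried.

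The size of any between-arm distortion is conditional. With equal testing there is essentially none. With a mean of 3 versus 2 extra draws the false-positive rate is about 12%, and with 4 versus 2 about 30% at an RR of about 1.15. These figures rest on an assumed 30% fall, log-SD 0.4, Poisson extra draws and no trend over time, and the direction could go either way. The primary endpoint and the total of 300 are untouched. The change should be made, but the trial does not depend on it.

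**What to change.** In Section 2.4.2, take item 6 out of the event list and limit the binary and time-to-event sentence to the clinical events. Define the laboratory endpoints as change from randomisation at the scheduled 48 h and 96 h samples, compared by means as in the synopsis. State that later values, taken at clinical judgement, are descriptive only. Align the Appendix 2 grid with its footnote at the same time, so that the two scheduled samples are unambiguous.

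The cost is a wording change, with no new visits, samples or patients. The downside is that values after 96 h are no longer used for inference between arms.
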